## Abstract

**Background:**

Dozens of scales and questionnaires have been used in the detection of frailty; however, a generalized method for its screening and diagnosis is still lacking in clinical settings. FRAILTOOLS´ main objective is to evaluate the usefulness of frailty scales in the detection of frailty in different clinical and social settings, and its integration in management algorithms for the frail older patient.

**Methods:**

FRAILTOOLS is an observational, longitudinal and prospective study with a follow-up of 6, 12 and 18 months. People older than 75 years old will be recruited from three separate clinical settings (acute geriatric wards, geriatric outpatient clinics and primary care) and one social setting (nursing homes). Exclusion criteria include Mini-mental State Examination < 20 points, and a Barthel index < 90 points, except in nursing home residents (< 40 points). The participants will be recruited in Spain, Italy, France, United Kingdom and Poland. The total sample size will be of 1.940 subjects, 97 subjects in each clinical setting by center. A personal interview with each participant will take place to register data on comorbidity (Charlson Index), functional (SPPB, Barthel and Lawton indexes), cognitive (MMSE) and frailty status (Fried Phenotype, Frailty Trait Scale – short version, SHARE-FI, 35-Items Rockwood Frailty Index, Clinical Frailty Scale, FRAIL scale and Gérontopôle Frailty Screening Tool) in the baseline visit, month 12 and month 18 visit of follow up. At 6 month a phone call will be made to assess whether there have been falls and to check the vital status.

**Discussion:**

Currently, the usefulness of certain assessment tools in social and clinical settings have not been properly assessed, including their ability to predict the individual risk for different adverse outcomes, which is the main interest in daily practice.

The FRAILTOOLS project concentrates on providing screening and diagnostic tools for frailty in those settings where its prevalence is the highest and where efforts in prevention could make a significant change in the trend towards disability.

**Trial registration:**

Comprehensive validation of frailty assessment tools in older adults in different clinical and social settings (FRAILTOOLS), NCT02637518 (date of registration: 12/18/2015).

## Background

From the second half of the twentieth century, life expectancy has increased in developed countries, reaching a mean age of 83 years in countries such as Spain, France and Italy [1, 2]. As a result, Europe is the continent with the highest proportion of older people, but also with a higher dependency ratio rate [2].

From a health and social point of view, the older population has increased requirements, needing specialized care to approach the complexity of their comorbidities [3]. On the other hand, as life expectancy increases, the proportion of older people with any kind of disability rises [4], which in turn increases the need for long term care facilities. All of this leads to additional health and social expenditure [2].

In order to address this situation, new policies are needed, which are particularly aimed at: a) implementing reforms in the pension system, health and care and long-term care facilities, and b) reducing disability and dependency. As to the latter, it is imperative to detect the population at higher risk of disability, with the objective of implementing preventive actions [1, 2].

Within the last 20 years, health and social care professionals dedicated to the field of geriatric medicine have made major efforts in identifying older people requiring specialized attention that may contribute to delay or avoid the appearance of disability. Prior to disability there is an intermediate state known as frailty, a syndrome characterized by diminished capacity to respond to stressors, due to a reduced functional reserve [3]. Frailty is a condition that is closely associated with mortality among community dwelling older adults, followed by organ failure, cancer and terminal dementia [5]. This condition is also related to other adverse outcomes such as: falls, morbidity, disability, polypharmacy, hospitalization, institutionalization and mortality [6].

Multiple studies have been undertaken worldwide to establish the prevalence of frailty [3, 7–9]. The data vary according to countries reaching a percentage of up to 27.3%. A survey of 7510 community-dwelling older adults in 10 European countries found that the prevalence of frailty was higher in southern than in northern Europe [7, 10]. For instance, in Spain the prevalence of frailty was 8.4% among institutionalized and community dwelling persons from rural and urban settings [8]. In Italy, in community-dwelling older adults the frailty prevalence was 13.9% [11]. In the French population older than 55 years-old and free of disability, around 25% are either frail or multimorbid [12]. In the nursing home setting this prevalence doubles in comparison with community dwelling people, reaching 68.8% according to a number of American studies [9, 13]. As frailty is highly associated with age, we should expect an increase in the number of new cases (incidence) of frailty as the European population gets older. Published data ranges from 4% new cases in adults aged over 65 years in Germany to 8% in adults aged over 60 years in Spain after three years of follow-up [14].

Dozens of scales and questionnaires have been used in the detection of frailty [15].; however a universal operational definition of frailty or a generalized method for its screening and diagnosis is still lacking [16]. In different clinical scenarios where the care of the elderly is a priority, such as primary health care or nursing homes, it is imperative to have specific instruments in the detection of frailty according to the characteristics of each level of care.

The FRAILTOOLS Project addresses the needs to validate scales for its application in different clinical and social settings, and its integration in management algorithms for the frail older patient.

## Methods/design

### Objectives

#### Main objective

Evaluate the usefulness of frailty scales in the detection of frailty in different clinical and social settings.

#### Secondary objectives

Establish the scale with the highest predictive value according to the most common adverse outcomes in frail patients.Design frailty detection algorithms according to the clinical setting.

### Outcomes

#### Primary outcomes

Determine the predictive value of frailty scales according to the adverse outcomes associated with frailty in people older than 75 years old in different settings of clinical care.**Mortality:** Data will be obtained from the official registration of the country of the corresponding partner from a participant who does not answer the telephone or who does not have medical follow-up after the last visit.**Disability:** It will be defined as a loss of one point in the Short Physical Performance Battery (SPPB), the loss of independence in any Instrumental Activity of Daily Living (IADL) according to the Lawton index, or by a reduction in ≥5 points in the Barthel index [17–19].**Falls:** It is an event in which the participant comes to rest inadvertently on the ground or other lower level. Data will be collected by the participant’s verbal recall (self-assessed) and will be registered in the Query-Case Report Form (eCRF).**Incident cognitive impairment:** It will be defined by a reduction of ≥2 points in the MMSE [20].

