### Questionnaires and tools assessed

In the Query-Case Report Form the following information will be collected:Socio-demographic data: age, gender, race, marital status, education, cohabitation, need for caregiver, setting in which the subject is recruited, country of origin.Comorbidities:○ Charlson Comorbidity Index [22]: This scale predicts the ten-year mortality for a patient by classifying or weighting comorbid conditions. It consists of 19 issues each of which was weighted according to their potential influence on mortality.Functional status:○ Barthel Index [18]: Functional assessment scale that measures the subject’s capacity to perform ten activities of daily living in an independent manner.○ Lawton Index [17]: Instrument to assess the individual’s capacity to perform IADL independently. These skills are considered more complex than the basic activities of daily living as measured by the Barthel Index.○ Short Physical Performance Battery [23]: Test designed to measure functional status and physical performance by combining the results of the gait speed, chair stand and balance tests.Cognitive status:○ Mini Mental State Examination – MMSE [20]: It is a widely used test to screen patients for cognitive impairment and to track changes in cognitive functioning over time. It evaluates seven cognitive domains including orientation to time and place, repetition, verbal recall, attention and calculation, language and visual construction.Frailty assessment scales:○ Fried’s Frailty Phenotype Criteria [3]: Well-known scale to diagnose frailty. It is based on the biological causative theory and shows predictive validity for poor health outcomes across a wide range of illnesses and procedures. This tool combines a total of five variables, three of them self-referred: weight loss, exhaustion and reduced physical activity; and other two objective variables: weakness assessed by grip strength, and slowness measured by gait speed.○ Frailty Trait Scale – short version [24]: Scale that emerged from a population study in Toledo, Spain. It evaluates three dimensions: nutrition (BMI), physical activity (PASE), and nervous system (balance test).○ SHARE Frailty Instrument (6,7): Screening instrument for frailty proposed for the primary health care setting. It explores five dimensions: exhaustion, loss of appetite, weakness measured by grip strength, difficulty walking and low physical activity.○ 35-Items Rockwood Frailty index [25]: Scale with 35 items, based on data routinely collected as part of a geriatric assessment. It includes items on chronic diseases, basic and instrumental disabilities in activities of daily living, serum vitamin D, cognition, physical performance, nutrition, visual and hearing impairment.○ FRAIL scale [26]: Self-assessed short questionnaire, taking into account five different aspects: Fatigue, Resistance, Ambulation, Illness and Loss of weight. It does not require measurements or administration by healthcare professionals.○ Gérontopôle Frailty Screening Tool [27]: It is a short questionnaire addressed to primary care physicians with a total of six questions assessing the individual’s social, physical, functional and cognitive situation. There is no clear cut-off point to classify the patient as frail or not.○ Clinical Frailty Scale o Rockwood modified [28]: Scale that uses clinical descriptors and pictographs to stratify older adults according to level of vulnerability. It mixes items such as comorbidity, cognitive impairment and disability. According to the authors, it provides predictive information about mortality or institutionalization similar to that of other established tools.

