### Statistical analysis

FRAILTOOLS aims to 1) assess the selected instruments (scales) for both screening and diagnosis purposes in each of the four settings: acute geriatric wards, geriatric outpatient clinics, primary care centers and nursing homes; and 2) explore the sequential or consecutive assessment of the older population amongst settings.

Regarding the first objective of the analysis, we will assess the associations of each of the seven scales with the outcome for each setting and outcome through logistic regressions using age, sex and Charlson index as possible confounders. With these variables, we will construct three logistic regression models: unadjusted, adjusted by age and gender, and adjusted by age, gender and Charlson Index. Firstly, we will compute the classification performance (sensitivity, specificity, ROC curve, AUC, predictive values, likelihood ratios) for each model. This way, we will assess the most accurate scale for both screening (the most sensitive tool) and diagnostic purposes (the most specific tool), for each setting and for each outcome. Secondly, we will study the feasibility of the models, considering the time needed for the scale and the percentage of patients that can be evaluated per case.

Combining both outcomes by creating an index (classification performance * proportion of evaluated patients), we will determine the best scale (maximum value of the index) per setting for both screening and diagnosis. Thirdly, we will evaluate the sensitivity to change of the scales and the covariance of the scales with other measures as the SPPB through a mixed linear model.

For the second objective, we will first analyze the external validity of each model by using the data of each setting in the other models during the last phase of the project. Afterwards, we will evaluate which set of instruments is more appropriate for sequential or consecutive assessment when patients move between different settings: e.g. from nursing homes to geriatrics wards.

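### Disability and cognitive impairment are small losses from baseline, but no planned model accounts for the baseline score, so the ranking of scales can be biased in a direction that varies by setting

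*Protocol article*

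**What the plan says.** Under Primary outcomes, disability is met by any one of three changes. The SPPB limb is "It will be defined as a loss of one point in the Short Physical Performance Battery (SPPB"; the second is "the loss of independence in any Instrumental Activity of Daily Living (IADL) according to the Lawton index"; the third is "by a reduction in ≥5 points in the Barthel index". Incident cognitive impairment rests on the MMSE alone: "It will be defined by a reduction of ≥2 points in the MMSE".

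Under Statistical analysis, each of the seven scales is related to each outcome in each setting "through logistic regressions using age, sex and Charlson index as possible confounders". The models are then listed: "unadjusted, adjusted by age and gender, and adjusted by age, gender and Charlson Index". Sensitivity, specificity, AUC, predictive values and likelihood ratios are computed from them, and the most sensitive and most specific scales are chosen per setting and outcome. The sample size section assumes the same four variables.

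Table 2 schedules Barthel, Lawton, SPPB and MMSE at baseline, month 12 and month 18.

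Under Questionnaires and tools assessed, the scales overlap unequally with the outcome instruments. The 35-item index includes "basic and instrumental disabilities in activities of daily living, serum vitamin D, cognition, physical performance". Fried's criteria include gait speed and the Frailty Trait Scale a balance test, both of which are SPPB components. The Clinical Frailty Scale mixes disability and cognitive impairment. The FRAIL scale is self-reported and needs no measurement.

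**The concern.** Whether a person records a small loss depends partly on where the baseline score happened to fall. A baseline that is low by chance tends to be followed by a higher score. Someone at the bottom of a scale cannot lose a point; someone whose real capacity lies above the top can decline without its showing. Frail people sit lower on these instruments, so these artefacts become mixed with the frailty association.

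The effect is also unequal between scales. A chance-low SPPB or MMSE makes a scale that uses the same measurement read frailer and, at the same time, makes a recorded loss less likely. A questionnaire-only scale does not carry that shared error. Because the study's product is the choice of a best scale per setting and outcome, part of the ranking on these two outcomes could reflect item overlap rather than prognostic value.

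Separately, a fall from 30 to 28 on the MMSE counts as incident cognitive impairment, although it shows decline and not impairment.

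**Working it through.** **1. The plan's own figures.** Four variables at 10 events each (the 10 is an assumption that reproduces the figures) give 40 events. The smallest n with n×0.15 − z×√(n×0.15×0.85) ≥ 40 is 355 for z = 1.96 and 388 for z = 2.576. Then 388/0.8 = 485, and 485×4 = 1940. All match. Death drives this calculation, so the present point does not touch it.

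**2. How often noise alone produces an event.** Assume no true change and an independent error SD e at each visit. Ignoring scale limits, a recorded loss of at least 1 point on a whole-point scale needs a difference above 0.5, and a loss of at least 2 needs one above 1.5.
- P(SPPB loss ≥1) = 1 − Φ(0.5/(√2·e)): 24% at e = 0.5, 31% at 0.7, 38% at 1.2.
- P(MMSE loss ≥2) = 1 − Φ(1.5/(√2·e)): 14% at e = 1.0, 24% at 1.5.

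**3. Where floors can and cannot operate (Exclusion criteria).** MMSE of 20 or below is excluded, so a 2-point loss is always possible. Barthel below 90 is excluded in the three clinical settings, so a 5-point loss is always possible there. Floors therefore concern SPPB and Lawton, mainly in nursing homes, where Barthel may be as low as 40. For the MMSE, regression to the mean and a ceiling remain.

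**4. Direction, with no true effect of frailty on decline.** The composite of all three instruments was simulated (error SD: SPPB 0.7, Lawton 0.4, Barthel 2). Clinic-like means were 8, 6.5 and 97, with Barthel entry at 90; nursing-home-like means were 4, 1.5 and 70, with entry at 40. A correct odds ratio per SD of the scale would be 1.

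| Population | OR without baseline | OR with baseline |
|---|---|---|
| Nursing-home-like | 0.74 to 0.82 | 1.08 to 1.11 |
| Clinic-like | 1.38 to 1.43 | 1.36 to 1.50 |

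For SPPB alone (SD 2.7, reliability 0.8 to 0.9, frailty correlated −0.5 with SPPB, scale sharing no error), the null odds ratio without baseline is about 0.9 near the floor, 1.06 at mean 8 and 1.2 at mean 10. With baseline it is about 1.2 to 1.4.

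**5. Ranking.** AUC without baseline for two simulated scales, the second using the measured baseline score:

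| Outcome, assumed error SD | No overlap | Overlap |
|---|---|---|
| SPPB mean 8, error 0 | 0.625 | 0.626 |
| SPPB mean 8, error 0.7 | 0.610 | 0.589 |
| SPPB mean 8, error 1.2 | 0.595 | 0.546 |
| SPPB mean 3, error 0.7 | 0.498 | 0.435 |
| MMSE, error 1.0 | 0.603 | 0.564 |
| MMSE, error 1.5 | 0.590 | 0.525 |

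A separate set-up (mean 8, reliability 0.8) gave 0.573 against 0.502, in the same direction. The clinic-like composite with a moderate true effect separated much less (0.701 against 0.696), so the penalty is not uniform.

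**6. Room for baseline terms.** About 485×0.8 = 388 per setting are evaluable. One extra covariate (MMSE) makes 5 variables, or 50 events: 50/388 = 12.9%. Three (SPPB, Barthel, Lawton) make 7, or 70 events: 70/388 = 18.0%. Under the plan's own 99% lower-limit rule the event rate must be higher: 388×0.179 − 2.576×√(388×0.179×0.821) ≈ 50, and 388×0.236 − 2.576×√(388×0.236×0.764) ≈ 70. That is about 18% and 24%.

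**The case against.** The strongest reply is that the aim is the predictive value of each scale as used in practice. An unadjusted model is right for that, and forcing baseline function into every model would remove the standalone performance a screening tool needs. It would also adjust away content that belongs to the 35-item index and the Clinical Frailty Scale. This stands: in the clinic-like null case, models containing baseline had AUCs of 0.594 to 0.598 whichever scale was used, so they no longer rank the scales on their own.

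A reader might also infer that omitting baseline masks the frailty association and pulls odds ratios toward 1 throughout, and that adjustment restores the truth. The article does not support that. With a moderate true effect, the clinic-like composite gave 2.20 without baseline and 1.75 with it for a non-overlapping scale, which is not masking. When a true odds ratio of 2.0 was simulated with frailty uncorrelated with SPPB, so that baseline could not matter, the observed value was 1.24 to 1.31 with or without baseline; most of that attenuation is outcome noise. And adjustment for an error-prone baseline created associations where none existed (section 4 of the check).

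Finally, an article leaves detail to the full plan. That covers component reporting and sensitivity analyses taken alone. It does not cover the model list, which the article states and from which the ranking follows.

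**Conclusion.** The concern holds in limited form. Two of four primary outcomes are small changes from baseline, and none of the three stated models accounts for the baseline score. The resulting bias can go either way by setting: downward near the SPPB and Lawton floors, upward near ceilings. Scales sharing function or cognition items with the outcome (35-item index, Fried, Frailty Trait Scale, Clinical Frailty Scale) can be ranked too low. In the SPPB-only and MMSE simulations with measurement error the AUC penalty ran from about 0.02 (0.610 − 0.589) to 0.07 (0.590 − 0.525), enough to change which scale is called best.

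These sizes rest on assumed reliabilities, baseline distributions and decline rates; the article gives none, so the actual distortion is unknown. Death and falls are not affected, nor is the sample size. The change should be made, but the planned models are not invalid for standalone prediction.

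**What to change.** 1. Keep the three planned models for standalone predictive value.
2. For disability and cognition, add by setting a baseline-only reference model (SPPB, Barthel and Lawton, or MMSE). Report each scale's gain over it as an additional analysis, not a replacement, and state that adjustment for an error-prone baseline can itself leave a spurious association.
3. Report the SPPB, Lawton and Barthel components separately, and identify participants who cannot lose a further point.
4. Add a sensitivity analysis that counts a loss only if it is present at both month 12 and month 18.
5. Call the MMSE outcome cognitive decline.

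No new data are needed, since Table 2 already schedules every score. The cost is more analysis work and fewer events in the confirmed-loss analysis. The baseline terms fit the planned sample size if the decline outcomes reach the frequencies shown in section 6 of the check.

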#### Secondary outcomes

**Performance** of the instruments by clinical setting: seven frailty assessment tools will be used in four different levels of care. The performance of each scale in the classification of frailty will be established.**Feasibility** composed by two main conditions: the percentage of people that are assessed by each tool in each setting (adequacy) and the time for carrying out the tool assessment. The utility of both screening and diagnostic tools stems, among other characteristics, from the time needed to pass them. This characteristic is relevant mainly in settings where the demand for attention is high and the time to provide is limited.**Sensitivity to change**, one of the problems of many of the tools used to assess frailty is that they have a low sensitivity to change. This is a relevant issue in clinical settings, where monitoring the progress of the patient is of high value. For this purpose, we will evaluate the change in the assessment level of patients observed at 12 and 18 months with each of the tools and their correlations with the changes observed in the functional status of the patients as assessed by SPPB.**Qualification as screening and/or diagnosis tool**: evaluate the utility of each scale as a frailty detection method, using pre-established criteria, based on the prevalence of this condition in each setting and the classification performance (Sensitivity, Specificity, Positive and Negative Predictive Values and Likelihood ratios), plus its feasibility, and its sensitivity to change.

